## **Methods**

### **Trial design**

A parallel two group randomized controlled clinical trial will be conducted to assess the use of ForeSite PT™ system on a pressure-related skin and tissue changes, with progression to pressure ulceration; interface pressure; and the perceptions of healthcare providers and patients to the ForeSite PT™ system. Eligible consenting inpatients will be randomly allocated to either have the ForeSite PT™ system and the LCD monitor turned on (intervention group), or have the ForeSite PT™ system and the LCD monitor turned off (control group) in a ratio of 1:1. Both groups will be included in the study up to a maximum of 7 days. Interface pressure and clinical outcomes will be measured at baseline (within 24 hours of admission) and on the last day of enrollment in the trial (within 24 hours prior to discharge, or on the seventh day (whichever comes first)). The perceptions of patients allocated to the intervention group, and the perceptions of healthcare providers each time a patient in their care is allocated to the intervention group, will be measured on the last day of enrollment in the trial or on the seventh day (whichever comes first).

Ethics ID number: REB13-0794

Study Title: Effectiveness of a pressure-sensing mattress system for reducing the risk of pressure ulcer formation by lowering interface pressure in vulnerable patient populations: Parallel-two-group randomized trial

PI: [name]

Version number/date: V2 01/04/2014

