## 190 **Outcomes**

### 191 **Primary Outcome**

- 192 1. A composite of interface pressure measurements that reflect the distribution of interface pressure  
193 at predetermined time intervals. These measures include:
- 194 a. proportion of participants that have pressure readings greater than 40 mmHg;
  - 195 b. average interface pressure (excluding sensels with 0mmHg reading); and
  - 196 c. the absolute number of sensels with pressure readings greater than 40 mmHg.

197 The measurement of this outcome will be facilitated by the ForeSite PT™ system's sensor overlay that  
198 continuously collects pressure readings. The array of the sensor overlay is a capacitive sensor with a  
199 0.625" spatial resolution. There are 52 rows x 118 columns for 6,136 sensing points. The ForeSite PT™  
200 system's software continuously samples interface pressure at a rate of 1 Hz, which can then be  
201 extracted for analysis. The data file is in a proprietary binary format, and can be exported to TXT or CSV  
202 formats for import into a spreadsheet program for analysis. This will be achieved by the sampling of  
203 pressure readings at specified time intervals before and after turning/repositioning when the ForeSite  
204 PT™ system's LCD monitor is turned on, and when it is turned off.

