### **Sample size**

A total of 600 patients will be recruited from Unit 36, Unit 58, and the ICU will be enrolled in the trial, in order to randomize 300 patients to each of the intervention and control arms. Sample size estimates for the primary outcome indicate a need for 294 patients in each of the intervention and control arms. This is based on an estimated control group event rate of 30%, an intervention group rate of 20% (i.e., a 33% relative risk reduction), an alpha level of 0.05, and 80% power.

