### **Randomization**

The random allocation of patients to intervention vs. control groups will be conducted following enrollment in the trial (i.e., admission to study settings). Allocation will be completed in a concealed manner by a research methodologist in the Calgary Institute for Population and Public Health at the University of Calgary, using a random number generator that will produce a randomization list organized in blocks of 6.

The list will be used to prepare sealed, opaque, allocation envelopes that will be stored in a secure documents cabinet in the clinical setting. The Research Nurse and Research Assistant will then access these envelopes in the secure storage area to determine patient allocation at the time of randomization.

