## 291 **Analysis and Statistical Methods**

292 Subjects will be stratified by their pressure ulcer risk, as determined by their Braden Score.

293 Data analysis will involve use of Chi-square and/or Fisher exact tests for between-group (i.e.,  
294 intervention and control groups) comparisons of the primary outcome and the secondary outcomes, and  
295 the Wilcoxon rank sum test for between-group comparison of strategic shifting. Chi square and t-tests  
296 will be used to compare baseline characteristics between groups, and logistic regression will be used for  
297 adjusted analyses if there are notable between-group differences for important baseline characteristics.  
298 Correlation between pressure distribution (the study's primary endpoint) with the hard clinical outcome  
299 (pressure ulceration and pressure-related skin appearance changes) will also be explored.

300 Univariate statistics will be used to summarize changes in pressure distribution as per the interface  
301 pressure feedback provided by the ForeSite PT™ system.

302 Univariate statistics will be used to summarize close-ended survey data, while open-ended survey data  
303 will be thematically analyzed.

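### The chi-square/Fisher tests named for the whole primary outcome do not fit its continuous and count components, (b) and (c), and the patient is not fixed as the unit of analysis for them

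*Protocol*

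**What the plan says.** **Unit of randomisation and sizing.** Under Randomization, allocation is by patient: "The random allocation of patients to intervention vs. control groups will be conducted following enrollment in the trial". The Sample size section also counts patients: "Sample size estimates for the primary outcome indicate a need for 294 patients in each of the intervention and control arms". It assumes event rates of 30% and 20%, alpha 0.05 and 80% power.

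**Primary outcome.** The Primary Outcome section defines a composite of three pressure measures taken at set times:
- (a) "proportion of participants that have pressure readings greater than 40 mmHg", a yes/no per participant;
- (b) the mean interface pressure over sensels that do not read zero, a continuous quantity;
- (c) "the absolute number of sensels with pressure readings greater than 40 mmHg", a count.

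The data come from a mat of 6,136 sensing points sampled at 1 Hz. The analysis data are to be "pressure readings at specified time intervals before and after turning/repositioning when the ForeSite" PT display is on, and when it is off. Trial design allows up to 7 days per patient.

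**Tests.** Analysis and Statistical Methods gives chi-square and/or Fisher exact tests for the between-group "intervention and control groups) comparisons of the primary outcome and the secondary outcomes". The Wilcoxon rank-sum test is kept for strategic shifting and t-tests for baseline characteristics. Logistic regression serves adjusted analyses. Changes in pressure distribution are otherwise only summarised descriptively.

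**The concern.** A test has been named for the primary outcome, and it does not match two of that outcome's three components. A chi-square or Fisher test compares counts of independent observations that fall into categories. A patient's mean pressure is not a category, and neither is that patient's number of sensels above 40 mmHg. The 40 mmHg threshold classifies a sensel or a reading. It does not classify a patient's mean or count.

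An analyst who follows the section literally for (b) or (c) has two routes:
1. Choose a cut-off for the patient's mean or count. None is stated, the choice could be made after seeing the data, and splitting a continuous measure or a count in two discards information.
2. Classify readings and tabulate arm by reading. Readings from one patient share body build, mattress and posture, so they are correlated and the test's independence assumption fails.

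The claim that the device lowers interface pressure rests on this outcome, so the choice of route should not be left open.

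**Working it through.** **1. The plan's own figure.** Inputs from the Sample size section: 30% and 20%, alpha 0.05 (two-sided assumed, since sidedness is not stated), power 80%. With pooled variance under the null and no continuity correction:

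n = [1.96 × √(2 × 0.25 × 0.75) + 0.8416 × √(0.30 × 0.70 + 0.20 × 0.80)]² / 0.10²
= (1.2002 + 0.5119)² / 0.01 = 293.2, rounded up to **294 per arm**.

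This matches the stated figure exactly. Power is 80.1% at 294 per arm and 80.9% at 300. The sizing is therefore a comparison of two proportions with one independent yes/no per patient.

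**2. Matching test to variable.**

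| Measure | Type | Chi-square/Fisher suitable? |
|---|---|---|
| (a) participants with readings above 40 mmHg | yes/no per participant | yes |
| (b) average pressure | continuous | no, unless cut at an unstated value |
| (c) sensels above 40 mmHg | count | no, unless cut at an unstated value |
| Skin and soft-tissue composite (secondary) | yes/no per patient | yes |

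**3. What pooling readings would do, if it were done.** With m readings per patient and intraclass correlation ICC, the variance is inflated by the design effect DE = 1 + (m − 1) × ICC. A nominal two-sided 5% test that ignores this has a true type I error of 2 × [1 − Φ(1.96 / √DE)]. The protocol gives neither m nor ICC, so every value below is an assumption.

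At ICC 0.05:
- m = 2: DE = 1.05, 1.96/√DE = 1.913, error 5.6%
- m = 4: DE = 1.15, 1.828, error 6.8%
- m = 14: DE = 1.65, 1.526, error 12.7%
- m = 84: DE = 5.15, 0.864, error 38.8%

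Range over ICC:

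| m | ICC 0.01 | ICC 0.05 | ICC 0.5 |
|---|---|---|---|
| 2 | 5.1% | 5.6% | 11.0% |
| 4 | 5.4% | 6.8% | 21.5% |
| 14 | 6.5% | 12.7% | 47.4% |
| 84 | 14.7% | 38.8% | 76.4% |

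**4. Simulation check.** Beta-binomial data with 300 patients per arm, 30% of readings above threshold in both arms and 2,000 runs gave 12.4% (m = 14) and 38.7% (m = 84) for the pooled test at ICC 0.05, in agreement with the formula. A t-test on one total per patient gave 4.1% to 6.0% in every scenario simulated.

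**The case against.** A reader might infer that the protocol plans to test readings or sensels as if they were separate subjects, and so carries a false-positive rate far above 5%. The documents do not support that:
- No section says that readings or sensels are the tested unit. Component (a), the 294-per-arm calculation, the reference to subjects in the analysis section and the use of logistic regression all point to the patient. On that unit chi-square is valid.
- Component (c) is already summed over sensels and (b) is averaged over them. An arm-by-sensel table is not what the outcome definition yields, so inflation figures based on thousands of sensels do not apply.
- Trial design has interface pressure measured at baseline and on the last day, which allows as few as two occasions. The two- and four-hourly turning intervals in the Background are outside recommendations and not this trial's sampling schedule. At 2 to 4 readings and ICC 0.05 the excess is under 2 percentage points.

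All of this stands. It removes any statement that the plan as written has an inflated error rate.

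It can also be said that reducing frames to one value per patient is ordinary statistical analysis plan content, and that plan is not shown. Silence on that step alone would be no finding. But the protocol is not silent on the test. It names one for the whole primary outcome, and at patient level that test cannot be applied to a mean or a count without a further rule. The mismatch is in the stated text and survives the objection.

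**Conclusion.** The point holds in a limited form. The named tests suit component (a) and the skin composite, but not (b) or (c), and the section does not fix the patient as the unit of analysis for those two. The mismatch follows from the text alone and needs no assumption.

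Its numerical consequence is conditional. With one yes/no per patient there is no inflation. If readings were pooled, type I error would lie between about 5% (2 readings, ICC 0.01) and 76% (84 readings, ICC 0.5) over the assumed values tabulated, and the protocol does not say where in that range the trial would fall. The information lost through an unstated cut-off is real but cannot be sized from the document, which gives no distribution for either measure.

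The wording should be corrected before analysis. It is not evidence that the planned analysis is invalid.

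**What to change.** In Analysis and Statistical Methods:
1. State that the patient is the unit of analysis for every pressure measure.
2. Reduce each patient's sampled frames to one value for (b) and one for (c), for example the mean over that patient's frames.
3. Compare those patient values between arms with a t-test or a Wilcoxon rank-sum test. Alternatively, keep the repeated readings and fit a mixed model or GEE with patient as the cluster and arm as the effect.
4. Keep chi-square/Fisher for outcomes with one yes/no per patient, namely component (a) and the skin composite.

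The cost is wording and slightly more analysis work. No extra patients or data are needed, and the 294-per-arm calculation for the yes/no event is unaffected. Confidence intervals will be wider than a pooled-reading analysis would show, and correctly so.

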Study Title: Effectiveness of a pressure-sensing mattress system for reducing the risk of pressure ulcer formation by lowering interface pressure in vulnerable patient populations: Parallel-two-group randomized trial

PI: [name]

Version number/date: V2 01/04/2014

component of prevention and treatment protocols. The best practices pertaining to a specific turning regiment varies from the National Pressure Ulcer Advisory Panel (NPUAP) recommending repositioning every two hours and the European Pressure Ulcer Advisory Panel (EPUAP) recommending every four hours. Thus pressure ulcer prevention and management are necessarily labour-intensive.

Continuous pressure imaging (or interface pressure mapping) of the interface pressure between the body and support surface could be an effective technology as part of an overall strategy for the prevention and management of ulcers. By placing a thin mattress or sensor pad with monitoring capabilities under a patient, pressure imaging interprets the interface pressures and provides the patient's real-time pressure points on a corresponding computer screen, which can assist healthcare providers determine when a patient should be re-positioned (Hanson). XSENSOR Technology Corporation designed the ForeSite PT™ Patient Turn System (here in "ForeSite PT™ system"), which can continuously monitor bed surface interface pressure and track the patient's exposure to that pressure. The ForeSite PT™ system provides patient turn tracking to assist with management of the patient turn schedule. The pressure exposure monitor provides a visual image that quantifies historical pressure information. The exposure monitor assists clinical staff by alerting them to the location of body areas that have experienced the greatest exposure to pressure. The surface pressure monitor provides clinical staff with a visual image of the pressure distribution across a patient's body. It can be used by care providers to identify high pressure areas in real time and to validate that patient repositioning has successfully relieved pressure.

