## **Objectives**

The primary objective of this study is to:

1. establish the effectiveness of a pressure-sensing mattress system (ForeSite PT™ system) in its ability to reduce interface pressure as reflected in a composite of pressure measurements.

Ethics ID number: REB13-0794

Study Title: Effectiveness of a pressure-sensing mattress system for reducing the risk of pressure ulcer formation by lowering interface pressure in vulnerable patient populations: Parallel-two-group randomized trial

PI: [name]

Version number/date: V2 01/04/2014

The secondary objectives are to:

1. assess whether the ForeSite PT™ system reduces the incidence of pressure-related compromised skin and soft tissues, with potential for progression to overt pressure ulceration;
2. determine the minimum interface pressure that is associated with higher risk for pressure ulcer development through the correlation of clinical outcomes and pressure outcomes;
3. assess healthcare provider and patient perceptions of the ForeSite PT™ system; and
4. establish the cost-effectiveness of the ForeSite PT™ system.

Specifically, the study will address the following research questions:

1. Is the ForeSite PT™ system effective at reducing interface pressure by assisting healthcare providers in determining the best method for patient turning/repositioning?
2. Does the use of the ForeSite PT™ system reduce the incidence of pressure-related compromised skin and soft tissues, with potential for progression to overt pressure ulceration?
3. Does interface pressure correlate with clinical outcomes?
4. Does the ForeSite PT™ system have more impact on the clinical outcomes of patients who have been identified as having a higher risk of pressure ulceration as per the Braden scale?
5. What are the perceptions (both positive and negative) of healthcare providers to the ForeSite PT™ system with regards to functionality, ease of use, and interpretation of pressure data on the computer monitor?
6. What are the perceptions (both positive and negative) of patients (and if appropriate, family members) to the ForeSite PT™ system (including sensor pad and monitor display of their pressure points)?

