## **Participants**

### ***Recruitment***

Identification of eligible inpatients will be facilitated by the charge nurse, the patient care manager, and nurses on their respective units, and by daily review of new admissions. After an eligible patient has been identified, the Research Nurse or the Research Assistant will ask him or her (or a substitute decision-maker, if not capable of consenting), if he or she would be interested in participating in a study to evaluate a pressure sensing technology that provides real-time feedback to healthcare providers. If the patient agrees to participate, he or she will be asked to provide informed consent. The Research Nurse will set up the ForeSite PT™ system, including placing the sensor overlay under the linen and mounting the LCD monitor to the headwall. The Research Nurse will ensure that the overlay and monitor are functioning properly on a daily basis, and will instruct housekeeping on sterilization practices of these device components.

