## 185 **Control Group**

186 Inpatients allocated to the control group will have the ForeSite PT™ system's LCD monitor turned off and  
187 hidden (i.e., real-time images of interface pressure will not be displayed on the monitor). As the ForeSite  
188 PT™ system will continue to sample interface pressure with the display turned off, this enables patients  
189 enrolled in the control group to undergo silent monitoring.

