### 205 **Secondary Outcomes**

Ethics ID number: REB13-0794

Study Title: Effectiveness of a pressure-sensing mattress system for reducing the risk of pressure ulcer formation  
by lowering interface pressure in vulnerable patient populations: Parallel-two-group randomized trial

PI: [name]

Version number/date: V2 01/04/2014

- 206 1. A composite of endpoints that reflect compromised skin and soft tissues, with potential for  
 207 progression to overt pressure ulceration. This will include:  
 208 a. skin discolouration;  
 209 b. localized tenderness without skin breakdown;  
 210 c. Stage I and II (partial thickness) pressure ulcer formation;  
 211 d. Stage III and IV (full thickness) pressure ulcer formation;  
 212 e. unstageable/Unclassified: Full thickness skin or tissue loss – depth unknown;  
 213 f. suspected Deep Tissue Injury – depth unknown; or  
 214 g. presence of any skin or wound infection (i.e., cellulitis, infected ulcers, or osteomyelitis).

215 This outcome will be measured by a head-to-toe skin clinical assessment for detection of pressure-  
 216 related skin changes and for overt ulceration by the Research Nurse. This assessment will be conducted  
 217 within 24 hours of admission and 24 hours prior to discharge, or on the seventh day (whichever comes  
 218 first). This information will be noted on a form, which requires the Research Nurse to circle the skin  
 219 areas where the patient may have skin changes or a pressure ulcer. They will label the circled area with  
 220 the numbers 1 to 9 that correspond to predetermined categories of pressure-related skin changes and  
 221 stages of pressure ulcer development.

222 The presence of a pressure ulcer and its severity, as well as the development of other skin condition  
 223 changes, will be determined as per the National Pressure Ulcer Advisory Panel's categories/staging  
 224 definitions (2,3,4,5,6,7) and other skin appearance changes (1,8,9) described below:

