### **Blinding**

The researchers, who will be involved in data analysis, including the Principle Investigator, Co-Investigators, and the Research Coordinator, will be blinded to treatment allocation. The Research Nurse and the Research Assistant will both be involved in participant recruitment, the randomization process, and data collection, and will not be blinded to treatment allocations. It will be impossible to blind

Ethics ID number: REB13-0794

Study Title: Effectiveness of a pressure-sensing mattress system for reducing the risk of pressure ulcer formation by lowering interface pressure in vulnerable patient populations: Parallel-two-group randomized trial

PI: [name]

Version number/date: V2 01/04/2014

289 participants and healthcare providers as they will be able to see if the LCD monitor that displays  
290 information about the patient's surface pressure on the bed is mounted to headwall.

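### The exploratory pressure-skin correlation is not separated by arm, and nothing keeps the unblinded skin rater from seeing the treatment-arm pressure map

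*Protocol*

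**What the plan says.** **The analysis.** Analysis and Statistical Methods announces a "Correlation between pressure distribution (the study's primary endpoint) with the hard clinical outcome" and describes it as exploratory ("pressure ulceration and pressure-related skin appearance changes) will also be explored"). It does not say whether the arms are taken together, separately or with adjustment for arm.

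**What it serves.** Secondary objective 2 is to "determine the minimum interface pressure that is associated with higher risk for pressure ulcer development through the correlation of clinical outcomes and pressure outcomes". Research question 3 asks whether pressure and clinical outcomes correlate.

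**Who rates the skin.** Secondary Outcomes assigns the head-to-toe examination, for pressure-"related skin changes and for overt ulceration by the Research Nurse", and has that nurse repeat it before discharge or on day 7. Under Blinding, the Research Nurse and Research Assistant take part in recruitment, "the randomization process, and data collection, and will not be blinded to treatment allocations". Only the researchers involved in data analysis are blinded.

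**What the rater can see.** Recruitment states: "The Research Nurse will ensure that the overlay and monitor are functioning properly on a daily basis". Under Treatment Group, the monitor shows real-time pressure images for the whole enrolment. Background describes the exposure display as helping staff by "alerting them to the location of body areas that have experienced the greatest exposure to pressure". Under Control Group, the monitor is off and hidden but sampling continues, which allows patients "enrolled in the control group to undergo silent monitoring".

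**The concern.** A correlation between a predictor and a rated outcome is interpretable only if the rating is made without reference to the predictor. In the treatment arm the rater has the predictor in view at the bedside. Several components of the skin outcome call for judgement: discolouration, tenderness, blanchable redness, and Stage I lesions, which the protocol's own table describes as hard to detect in dark skin. A nurse who has seen where pressure was highest may look harder there, or be readier to record a borderline finding.

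This differs from the usual worry about an unblinded assessor. Knowing the allocation threatens the comparison between arms. Seeing the patient's own map threatens the pressure-lesion association within the treatment arm. Blinding the analysts, or adding arm as a simple covariate, removes neither the exposure nor its effect on that association.

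At stake is the pressure threshold sought under secondary objective 2. The abstract presents the pressure-skin association as one of the trial's new contributions, with possible use in practice guidelines.

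**Working it through.** **The plan's own figure.** The plan gives no figure for the correlation. Its one sample size figure, 294 per arm, reproduces with 30% against 20%, two-sided 0.05 (sidedness assumed), 80% power, pooled variance and no continuity correction:

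[1.96 × √(2 × 0.25 × 0.75) + 0.8416 × √(0.3 × 0.7 + 0.2 × 0.8)]² / 0.10² = (1.2002 + 0.5119)² / 0.01 ≈ 293.1, rounded up to 294.

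This point leaves that figure unchanged.

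**Step 1: the exposure, side by side.**

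| | Treatment arm | Control arm |
|---|---|---|
| Skin rater | Research Nurse, unblinded | Research Nurse, unblinded |
| Daily monitor check by the same nurse | yes | yes |
| Map on display | yes | no, off and hidden |
| Pressure recorded for analysis | yes | yes |
| Stated masking of the map at the skin examination | none | not needed while the screen is off |

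The control-arm column assumes that the daily check does not involve switching the image on. The protocol does not say how the check is done with the screen off.

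**Step 2: an illustration.** Every input below except the 300 per arm is an assumption. Take a true lesion rate of 30% unrelated to pressure, a median split on pressure, and 300 patients per arm, so each pooled pressure half also has 300. Let the nurse detect 70% of lesions without guidance. Observed rate = 0.30 × detection. Each pooled half averages the two arms, and the control arm stays at 0.21 in both halves.

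With pL and pH the pooled rates in the lower and upper halves, SE = √[pL(1−pL)/300 + pH(1−pH)/300] and z = (pH − pL)/SE. The chance of a significant result is Φ(z − 1.96) + Φ(−z − 1.96).

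| Display-arm detection, low / high pressure | Display-arm rates | Pooled rates | Pooled OR | Chance of a significant result |
|---|---|---|---|---|
| 70% / 80% | 0.21 / 0.24 | 0.210 / 0.225 | 1.09 | 7.3% |
| 70% / 90% | 0.21 / 0.27 | 0.210 / 0.240 | 1.19 | 14.2% |
| 60% / 90% | 0.18 / 0.27 | 0.195 / 0.240 | 1.30 | 26.7% |

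The last row also needs low-pressure detection in the display arm to fall below the 70% kept for controls. The control arm alone stays at OR 1.0 and 5% in every row.

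A second illustration works on a continuous scale: 25% event rate, no true association, and in the display arm recording odds multiplied by 1.22, 1.49 or 2.01 per standard deviation of pressure seen. By simulation the pooled correlation is 0.04, 0.08 or 0.14. The chance of significance at 600 patients is about 18%, 54% or 94%. The control-arm correlation stays at 0. The distance between the two sets of results shows how far the answer depends on the assumptions.

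**Step 3: a case in which the bias vanishes.** Both illustrations let detection vary between patients according to pressure. The map, however, shows relatively high-pressure sites in every patient, and the measures listed under Primary Outcome (average pressure, count of sensels above 40 mmHg) are patient-level. If viewing the map raised detection to 80% in all display-arm patients, both pooled halves would read (0.24 + 0.21)/2 = 0.225 and the OR would be 1.0. If the display also lowered pressure, treatment patients would gather in the lower half and the same uniform rise would push a pooled association downward. So the direction is open as well as the size.

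**Step 4: the precision cost of reporting by arm.** Near r = 0, SE ≈ 1/√n: 1/√600 = 0.041 and 1/√300 = 0.058. The 95% half-width on the Fisher scale is 1.96/√597 = 0.080 against 1.96/√297 = 0.114. The correlation detectable with 80% power is tanh(2.8016/√597) = 0.114 against tanh(2.8016/√297) = 0.161.

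**The case against.** The strongest objections are these.

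- **A reader might infer that the protocol pools the arms.** It does not say so. It names no arm restriction, so a single analysis is the natural reading, but analysis by arm could be set in an analysis plan that is not shown. This stands, and silence on pooling alone would be no finding.
- **A reader might infer that the nurse uses the map to rate skin.** The protocol has the nurse verify that the equipment works, not read the map for the examination. The examination is head-to-toe, at fixed times, with numbered and described categories, which limits selective searching. This also stands: the documents show an opportunity only.
- **The illustrated figures rest on assumed detection rates applied between patients, while the mechanism acts between body sites.** This stands, and Step 3 shows that the bias can disappear under another assumption.
- **The control arm need not become the sole main data set.** This is right. Doing so would halve the sample and discard the arm in which the device may shift the pressure range.

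What the objections do not remove is the bedside condition. Who rates, and what that person can see, is fixed by this protocol. An analysis plan can separate the arms afterwards, but it cannot mask a map that was already in view.

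**Conclusion.** The point holds in limited form. In the treatment arm the skin rating is not protected from knowledge of the pressure with which it will be correlated. In the silently monitored control arm it is, provided the daily check there leaves the image off. The protocol neither masks the display at the examination nor separates the arms in the correlation that carries secondary objective 2.

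The documents do not support saying that the correlation is inflated, that half the sample is biased, or that any particular false-positive rate applies. The figures of 7% to 27%, and of 18% to 94%, are consequences of assumed inputs, and neither size nor direction can be derived from the plan. The consequence falls on an exploratory analysis. The primary comparison rests on sensor readings, and neither it nor the sample size is affected. The change is still worth making, because it is cheap and its bedside part cannot be added after data collection.

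**What to change.** 1. **Secondary Outcomes (both descriptions of the skin assessment):** require that the display be covered or blanked during the final head-to-toe examination, and that the skin form be completed before the map is viewed that day.
2. **Analysis and Statistical Methods:** state that the pressure-skin correlation and any pressure threshold will be reported separately by arm, or from a model with an arm-by-pressure term, with the control-arm estimate shown as the check free of map-guided rating.

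**Cost:** a few sentences, with no extra staff or visits. Per-arm estimates are less precise, as Step 4 shows. Covering the screen costs no precision, but it reduces rather than removes the influence of earlier daily viewing, which is why the by-arm report is needed as well.
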